
#### Determination of workload

For the standardized group, the workload will be determined based on %HRR and completed based on the following calculation:$$ \mathrm{H}\mathrm{R}\mathrm{R}=\left[\left(\mathrm{Maximal}\kern0.5em \mathrm{H}\mathrm{R}\hbox{-} \mathrm{Resting}\kern0.5em \mathrm{H}\mathrm{R}\right)\times \mathrm{Desired}\kern0.5em \mathrm{Percentage}\right]+\mathrm{Resting}\kern0.5em \mathrm{H}\mathrm{R} $$

For the individualized group, the workload will be determined based on ventilatory threshold values as previously described [5, 20] to determine VT1 and VT2. The criteria used for determining VT1 and VT2 will be a visual analysis of figures of time plotted against the relative respiratory variable – ventilatory equivalents of oxygen (VE/VO_2_) and ventilatory equivalents of carbon dioxide (VE/VCO_2_). Determination of VT1 will be an increase in VE/VO_2_ with no increase in VE/VCO_2_ and moving away from linearity of VE, whereas VT2 will be a simultaneous increase in both VE/VO_2_ and VE/VCO_2_. Calculations of HR values associated with ventilatory threshold (VT) values will be calculated prior to exercise sessions and with following HR ranges:Target HR > VT1 = HR range of 10 bpm below VT1 to the HR at VT1Target HR ≥ VT1 to < VT2 = HR range of 15 bpm above VT1 and below VT2Target HR ≥ VT2 = HR range of 10 bpm above VT2

Exercise volume will be prescribed based on energy expenditure per kg of body weight a week (kcal · kg^−1^ · week^−1^) to implement an isocaloric exercise volume (i.e., in terms of kilocalories [kcal] per kg a week) across individuals and groups. Previous research has found that energy expenditure ranging from 4 kcal · kg^−1^ · week^−1^ [21] to 23 kcal · kg^−1^ · week^−1^ [22–25] have positive effects on CRF and cardiometabolic responses to exercise. Therefore, this study will utilize a similar 12-week exercise protocol as previously described [5], while implementing a standardized isocaloric volume (kcal · kg^−1^ · week^−1^) instead of a designated time for each exercise session. Exercise progression will follow standard guidelines that have been previously established [4]. Figure 2 illustrates the exercise progression following baseline testing through the 12-week intervention for both experimental groups while Tables 1 and 2 show the SPIRIT study schedule for experimental and control participants, respectively.

**Fig. 2 Fig2:**
[figure not shown]
A detailed flow schematic of the exercise prescription for the experimental groups. *HRR* heart rate reserve, *kcal* kilocalories, *kg* kilograms, *VT1* first ventilatory threshold, *VT2* second ventilatory threshold

#### Time course changes over 12 weeks

Currently, there is no literature investigating the time course changes of VO_2_max and cardiometabolic risk factor values between a standardized and individualized CRF exercise program. Therefore, since testing will occur every fourth week, the time course changes over the first 12 weeks of the CRF training intervention will be highlighted and addressed. These data will help further analyze the incidence of response during 12 weeks of structured CRF training and gain insight into the time course changes associated with CRF training for each individual and based on the CRF training intensity (standardized or individualized).

#### Categorizing responders and non-responders

Following the 12-week intervention, the participants will be categorized as responders and non-responders (see statistical analysis section for further details) for each testing measurement. While each testing measurement will be evaluated, the overreaching categorization of responder and non-responder will be based on VO_2_max due to the profound health and performance implications of this measurement.

#### Modifying the prescription of non-responders

For the participants that are categorized as responders after the initial 12 weeks, they will be completed with the study. However, participants that were non-responders based on VO_2_max changes will be asked to complete a subsequent 12-week intervention. During this second 12-week intervention, participants will switch their exercise intensity prescription (i.e., if a participant in the standardized group was categorized as a non-responder, they will complete the second 12 weeks in the individualized group). The experimental design including the exercise prescription and testing (baseline and post-testing) will follow the same schedule and protocol. However, during week 4 and 8 the testing sessions will not include blood analysis. The SPIRIT study schedule for the second 12-week intervention can be seen in Table 3.

At the completion of the second 12-week intervention, the participants will again be categorized as responders or non-responders based on the new baseline and 12-week testing values. This crossover design intervention will help to gain insight on whether or not ‘non-responders’ can become responders if the intensity of the exercise prescription is modified.

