### Research aims

The objective of this research is to determine the incidence of response to VO_2_max after implementation of a standardized (%HRR) and individualized (based on first ventilatory threshold [VT1] and second ventilatory threshold [VT2]) approach to exercise prescription in a community wellness program for 12 weeks. The primary measurement outcome will be VO_2_max with secondary outcomes of total cholesterol (TC), high-density lipoprotein (HDL), low-density lipoprotein (LDL), triglycerides, blood glucose, and resting heart rate (HR) and blood pressure (BP). Thus, the main research aim is to determine whether an individualized exercise prescription decreases the incidence of non-response to CRF and cardiometabolic measurements compared to the standardized approach. Similarly, another primary research aim is to determine if changing the prescription of CRF intensity for a subsequent 12-week intervention elicits more responsiveness in previously categorized non-responders (based on VO_2_max responses). A key secondary aim of this research is to establish whether there are differences in the time course changes of VO_2_max and cardiometabolic risk factors between the experimental groups every fourth week during the 12-week intervention.

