**Fig. 1 Fig1:**
[figure not shown]
Schematic illustration of the research design

**Table 1 Tab1:** SPIRIT study calendar for the experimental group for the first 12-week intervention

			Exercise intervention				
Point of time:	Pre-intervention	Baseline	Time 0	Week 4	Week 8	Week 12	12-week analysis
Enrollment							
Recruitment	x						
Medical history	x						
Inclusion criteria	x						
Randomization			x				
Testing							
Height		x		x	x	x	
Weight		x		x	x	x	
Resting heart rate		x		x	x	x	
Resting blood pressure		x		x	x	x	
Waist circumference		x		x	x	x	
Low-density lipoprotein		x		x	x	x	
High-density lipoprotein		x		x	x	x	
Triglycerides		x		x	x	x	
Blood glucose		x		x	x	x	
Maximal exercise test		x		x	x	x	
Verification test		x		x	x	x	
3-day nutrition recall		x				x	
Analysis							
Biological variability			x				
Time course changes							x
Incidence of response							x

*SPIRIT* Standard Protocol Items: Recommendations for Interventional Trials

**Table 2 Tab2:** SPIRIT study calendar for the control group for the first 12-week intervention

Point of time:	Pre-intervention	Baseline	Time 0	Week 4	Week 8	Week 12	12-week analysis
Enrollment							
Recruitment	x						
Medical history	x						
Inclusion criteria	x						
Testing							
Height		x		x	x	x	
Weight		x		x	x	x	
Resting heart rate		x		x	x	x	
Resting blood pressure		x		x	x	x	
Waist circumference		x		x	x	x	
Low-density lipoprotein		x		x	x	x	
High-density lipoprotein		x		x	x	x	
Triglycerides		x		x	x	x	
Blood glucose		x		x	x	x	
Maximal exercise test		x		x	x	x	
Verification test		x		x	x	x	
3-day dietary recall		x				x	
IPAQ		x		x	x	x	
Analysis							
12-week changes							x

*SPIRIT* Standard Protocol Items: Recommendations for Interventional Trials, *IPAQ* International Physical Activity Questionnaire

**Table 3 Tab3:** SPIRIT study calendar (second 12 weeks) for VO_2_max non-responders after the first 12-week intervention

			Exercise intervention				
Point of time:	Pre-intervention	Baseline	Time 0	Week 4	Week 8	Week 12	12-week analysis
Pre-intervention							
Switch of experimental group	x						
Testing							
Height		x		x	x	x	
Weight		x		x	x	x	
Resting heart rate		x		x	x	x	
Resting blood pressure		x		x	x	x	
Waist circumference		x		x	x	x	
Low-density lipoprotein		x					
High-density lipoprotein		x					
Triglycerides		x					
Blood glucose		x					
Maximal exercise test		x		x	x	x	
Verification test		x		x	x	x	
3-day nutrition recall		x				x	
Analysis							
Incidence of response							x

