#### Biological variability

Intraclass correlation (ICC) of variation, typical error and co-efficient of variation (CV) for VO_2_max, resting HR, resting BP, and fasting blood glucose, total cholesterol, HDL, and LDL will be calculated as described previously [26]. The CV will be combined with the measurement error of the testing to determine the TE. The TE will be used to categorize responders and non-responders. In summary, for all criteria tested the changes in pre- to post- intervention will be analyzed with responders having a change > TE and non-responders having a change that is ≤ TE.

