### Limitations

There are several limitations that merit discussion. It is possible there may be heterogeneity in training responses due to age alone given the large age range (30 to 75 years) that will be recruited for the current trial. However, the age range for the target sample will be comparable to previous studies [22, 23, 33] and also reflect the likely age range found in community exercise programs [46]. Another possible limitation is external validity given data collection will take place at moderate altitude. Nevertheless, to the best of our knowledge, there is no evidence to suggest differences in training responsiveness (i.e. responders and non-responders) between altitude-residing individuals and sea level counterparts. A third potential limitation is the inability to anticipate how many participants will be categorized as non-responders following the first 12-week intervention. Indeed, this limitation could arguably be the most significant due to the second part of the trial (crossing over non-responders to the other prescription group) being underpowered if there are a low number of non-responders. Nevertheless, to our knowledge, there are no previous investigations evaluating a crossover design to determine if non-responders can become responders with a different exercise prescription protocol. Therefore, even if the second part of the trial is underpowered, the results would provide valuable preliminary insight into the efficacy of individualized exercise prescription.

In summary, this original randomized controlled trial aims to (1) investigate the efficacy of an individualized exercise prescription at improving training responsiveness and, (2) to better understand the time course changes of training adaptations to both individualized and standardized exercise intensity prescription methods. It is anticipated that findings from this novel trial will add to our knowledge of how personalized exercise can enhance training efficacy and limit training unresponsiveness.

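### With every first-stage non-responder switched and none kept on the first prescription, the second primary aim cannot separate the changed prescription from 12 more weeks of training; Table 3 and the text also disagree on second-stage bloods

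*Protocol article*

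**What the plan says.** Research aims gives the second stage primary status: "another primary research aim is to determine if changing the prescription of CRF intensity for a subsequent 12-week intervention elicits more responsiveness" in those first categorized as non-responders. The abstract lists the same question among four main outcomes.

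Modifying the prescription of non-responders sets the procedure. Responders leave the study, while "participants that were non-responders based on VO_2_max changes will be asked to complete a subsequent 12-week intervention". All of them change arm: "During this second 12-week intervention, participants will switch their exercise intensity prescription". At the end, "participants will again be categorized as responders or non-responders based on the new baseline and 12-week testing values". The rule is the one in Biological variability: "responders having a change > TE and non-responders having a change that is ≤ TE".

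The only untreated comparison is the control group. It is a separately recruited cohort asked to keep its usual activity, and its calendar (Table 2) covers the first 12 weeks only.

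Limitations acknowledges that the second stage may be underpowered, then says that even so "the results would provide valuable preliminary insight into the efficacy of individualized exercise prescription".

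On blood tests, the text keeps the first-stage baseline and post-test schedule with one exception: "during week 4 and 8 the testing sessions will not include blood analysis". The matching calendar, Table 3 ("SPIRIT study calendar (second 12 weeks) for VO_2_max non-responders after the first 12-week intervention"), marks LDL, HDL, triglycerides and glucose in the baseline column only. The non-blood tests are also marked at week 12.

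**The concern.** A participant enters the second stage because of a small observed change, is switched, trains for another 12 weeks and is then re-classified. If the second change exceeds TE, two explanations are available: the new prescription worked, or 12 further weeks of training would have been enough anyway. Choosing between them requires knowing how non-responders do when they continue unchanged, and no one in the trial supplies that. A larger second stage would estimate the mixture more precisely without separating its parts, so the admission of low power does not cover the problem.

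At stake is the reading of a stated primary aim. A high conversion rate could be reported as evidence for modifying the prescription when the design cannot attribute it to the modification.

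The blood-test mismatch is a smaller, separate matter. If staff follow Table 3, no second-stage change in lipids or glucose can be computed, and the missing samples cannot be recovered later.

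**Working it through.** **Plan's own figure.** The article gives no second-stage size, response rate or TE value, so there is nothing to reproduce for that stage. The first-stage target is 16 per group, and 16 / (1 − 0.20) = 20 with dropout. It enters here only as 2 × 16 = 32 evaluable trained participants.

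**Who could supply the comparison.**
- Non-responders staying on the first prescription: none.
- Control cohort: not training, not randomized, scheduled for 12 weeks. It can indicate test noise over 12 weeks but not the effect of further training.
- The two switch directions against each other: both groups are switched and both are selected after randomization, so the contrast does not isolate switching.

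**Inputs assumed.** Let σ be the within-person SD of one VO2max test, with independent errors and a fresh second-stage baseline. Write TE = kσ. The document fixes no k, so k = 1 to 2 is shown. A change score has SD √2·σ.

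**Noise alone (no true second-stage change).** P(change > TE) = 1 − Φ(k/√2).
- k = 1: 1 − Φ(0.707) = 0.240
- k = 1.41: 1 − Φ(1.00) = 0.159
- k = 2: 1 − Φ(1.414) = 0.079

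**Continued training on the same prescription.** Suppose everyone truly gains g TE in each block. With a fresh baseline the second-stage change is independent of the first-stage error, so P(convert) = 1 − Φ(k(1 − g)/√2). The share who are non-responders at stage 1 is Φ(k(1 − g)/√2). With k = 1:

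| True gain per block | Stage-1 non-responders | of 32 | Convert with no switch |
|---|---|---|---|
| 1 TE | 50% | 16 | 50% |
| 1.5 TE | 36% | about 12 | 64% |
| 2 TE | 24% | about 8 | 76% |

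Simulation of 1,000,000 people agrees (0.498, 0.639, 0.760).

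**Sensitivity, by simulation, for gains of 1, 1.5 and 2 (fresh baseline throughout).**
- True gains varying between people with SD 1 TE: 39%, 48%, 57%.
- Second block yielding half the first block's gain: 36%, 43%, 50%.
- Gains kept at 1, 1.5 and 2 test SDs but threshold raised to 2 SDs: 24%, 36%, 50%.

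In every case a substantial share converts with no change of prescription. The share depends on quantities that the trial does not observe in non-responders who continue unchanged.

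**Blood tests.** The text removes them at weeks 4 and 8. Table 3 removes them at weeks 4, 8 and 12. The dietary-recall row of the same table keeps both its baseline and week-12 marks, so the empty week-12 cells for bloods do not look like a table-extraction fault.

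**The case against.** Several points on the other side stand.

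- *Test noise is not wholly inseparable.* The repeat-test data behind TE and the controls' 12-week changes give a rough benchmark. The gap that no data in the trial can fill is continued training.
- *The size of the noise rate is uncertain.* A reader might take 24% as a fixed, guaranteed false-conversion rate. The article does not support that. It builds TE from the test-retest coefficient of variation combined with separately sourced equipment error, so the threshold may well exceed one test SD. At 2 SDs the rate is about 8%.
- *Regression to the mean.* A reader might infer that selecting low changes inflates the next change through test error. That would need the week-12 test that defined non-response to serve again as baseline. The text speaks of a new baseline and Table 3 schedules its own maximal and verification tests, so the natural reading is a fresh test. With independent errors, error-driven regression is then absent. The wording does not rule reuse out expressly, so one clarifying sentence is worthwhile.
- *Some wording is already modest.* The section on modifying the prescription promises only insight, and Limitations calls it preliminary. The stronger claims are in Research aims and the abstract, and Limitations still ties the result to efficacy.
- *A stay-or-switch randomization is not practical.* Assuming 24% versus 60%, it needs about 29 per arm for 80% power (two-sided 0.05), against 32 evaluable trained participants in total. It is not asked for.
- *The bloods do not affect the main classification.* Second-stage response is judged on VO2max.

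None of this supplies a comparator for 12 more weeks on the first prescription.

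**Conclusion.** The concern holds in a limited form. As designed, the second stage can describe how many first-stage non-responders respond after a switch plus 12 more weeks. It cannot attribute that proportion to the switch, whatever the sample size, and Limitations does not say so.

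The illustrative sizes rest on assumed values because no TE is given. Noise alone produces about 24% down to 8% for TE of 1 to 2 test SDs. Uniform true gains of 1 to 2 TE per block with TE = 1 SD produce 50% to 76% conversion on an unchanged prescription, and less if gains vary between people or shrink in the second block. These figures show that a sizeable rate would not be informative about switching; they do not predict the trial's result.

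The disagreement between Table 3 and the text on week-12 bloods is real but minor. It affects second-stage lipid and glucose change only.

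**What to change.** 1. In the abstract and Research aims, restate the second-stage aim as descriptive: the proportion of first-stage non-responders who respond after switching prescription and training for 12 further weeks, with an exact confidence interval. Say in Limitations that the effect of changing the prescription is not identified, in addition to the point about power.
2. If a noise benchmark is shown, take it from the trial's own TE data or from the controls' rate under the same rule, and state that it does not cover continued training. Do not use a fixed percentage.
3. State that the second-stage baseline is the separate test scheduled in Table 3, not the week-12 test that defined non-response.
4. Reconcile Table 3 with the text on second-stage blood tests at week 12.

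Items 1 to 3 are wording. Item 4 is a correction to the calendar or the text and, if bloods are taken at week 12, a few test cassettes. The real cost is that the second stage supports a weaker claim.

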### Data and confidentiality management

Electronic data will be coded, entered, and stored into a secure (password-protected) database on Western State Colorado University’s campus. All paper data, including consent forms, medical history documents, and daily exercise logs, will be stored in a secured locked cabinet in the Western State Colorado University Human Subject’s office. Only the primary investigators will have access to the data.

Due to the nature of the study, participants will be exercising in an environment with other members from the study. Therefore, anonymity of identity cannot be guarantee throughout the study. However, no research participant will be able to see or access any personal information – medical documents, exercise log, medications, etc. To ensure participant safety when exercising, researcher assistants delivering the exercise will be informed of relevant information that may influence how the participant responds to exercise. Any data collected and displayed in results of scientific manuscripts will be displayed in a way which does not disclose individual identity.

### Statistical analysis

All analyses will be performed using IBM SPSS Version 22.0 (Armonk, NY, USA) and GraphPad Prism 6.0 (GraphPad Software, San Diego, CA, USA).

#### Biological variability

Intraclass correlation (ICC) of variation, typical error and co-efficient of variation (CV) for VO_2_max, resting HR, resting BP, and fasting blood glucose, total cholesterol, HDL, and LDL will be calculated as described previously [26]. The CV will be combined with the measurement error of the testing to determine the TE. The TE will be used to categorize responders and non-responders. In summary, for all criteria tested the changes in pre- to post- intervention will be analyzed with responders having a change > TE and non-responders having a change that is ≤ TE.

#### Time course changes

Measures of centrality and spread will be presented as mean ± standard deviation (SD) and ranges will be reported for each measure. The precision of estimates will be reported as 90% confidence limits. Baseline-dependent variables will be compared using general linear model (GLM) ANOVA and Tukey post hoc tests, when applicable. Because baseline and every fourth week program data will be available after the completion of the first 12 weeks the effect of training on CRF (VO_2_max) and cardiometabolic measurements (TC, HDL, LDL, resting BP, and resting HR) will be determined using repeated-measures GLM-ANOVA with the exercise intensity (individualized or standardized) as the between subjects factor. Between group 12-week changes will be analyzed using GLM-ANOVA and Tukey post hoc tests, when appropriate. The assumption of normality will be tested by examining normal plots of the residuals in ANOVA models and will be regarded as normally distributed if Shapiro-Wilk tests are not significant [12]. Effect sizes will be calculated using means and pooled standard deviations. Method of data analysis will be analysis by treatment administered. Only participants who complete ≥ 70% exercise training sessions and strictly adhere to target exercise intensity will be included in the statistical analysis. The probability of making a type I error will be set at *p* ≤ 0.05 for all statistical analyses.

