### Sample – control group

Due to moral and ethical issues related to excluding participants from an exercise intervention to improve health, a control group will be recruited as a separate cohort. The control group participants must meet the same inclusion criteria and will not be allowed in the study if they meet the exclusion criteria, as previously mentioned.

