### Intervention

#### Testing

Testing sessions for both the experimental and control groups will be conducted at baseline and every fourth week during the 12-week intervention period. Testing sessions every fourth week will help to establish the current physiological levels to develop the exercise prescription for the experimental groups.

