#### Incidence of response

Delta values (Δ) will be calculated (post-testing minus baseline value divided by baseline value) for percent change in relative VO_2_max, TC, HDL, LDL, resting BP and resting HR and participants will be categorized as: ‘1’ = responder (% Δ > TE) or ‘0’ = non-responder (% Δ ≤ TE). Chi-squared (*χ*
^2^) tests will be subsequently used to analyze the point prevalence of responders and non-responders to exercise training separated by exercise intensity group (individualized and standardized) between baseline and the end of the end the first 12-week intervention. Only participants who complete ≥ 70% exercise training sessions and strictly adhere to target exercise intensity will be included in the statistical analysis. The probability of making a type I error will be set at *p* ≤ 0.05 for all statistical analyses.

In order to make inferences about the true values (population values) of the effect of both exercise interventions on VO_2_max and cardiometabolic factors, the uncertainty in effect will be expressed as 90% confidence limits and the likelihood the true value of the effect represents a substantial and clinically meaningful change (harm or benefit). Effects will be declared unclear if the confidence interval overlapped thresholds for substantiveness or the effect could be substantially positive and negative or beneficial and detrimental. All probabilistic magnitude-based inferences will be calculated using a published spreadsheet [27].

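### The visit effect of the two-arm repeated-measures model is not an effect of training, and the controls' week-4 and week-8 tests have no stated analysis

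*Protocol article*

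**What the plan says.** In the protocol article, Statistical analysis, Time course changes, the estimand and the model stand in one sentence. Its subject is the effect of training, on VO2max first and then on the other outcomes: "cardiometabolic measurements (TC, HDL, LDL, resting BP, and resting HR) will be determined using repeated-measures GLM-ANOVA with the exercise intensity (individualized or standardized". That two-level pair is the only factor between participants that the sentence names. The next sentence plans an ANOVA of between-group 12-week changes with Tukey tests where appropriate. The Statistical analysis section nowhere names the control group.

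Under Sample – control group, "a control group will be recruited as a separate cohort". Controls are therefore not randomised against the exercise arms. Under Testing, "Testing sessions for both the experimental and control groups will be conducted at baseline and every fourth week during the 12-week intervention period".

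The study calendars assign analyses by group. Table 1 (experimental) lists "Time course changes" among its analyses. Table 2 (control) lists only "12-week changes".

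**The concern.** A model whose only groups are two exercising arms can compare the two prescriptions. It cannot separate training from anything else that moves results between visits, such as familiarity with the maximal treadmill and verification tests. Yet the text gives this model the job of determining the effect of training.

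If the visit effect is reported that way, a shared retest change would appear as benefit from both programmes and as speed of adaptation. The exposure is greatest at weeks 4 and 8, where no control comparison is stated although the control tests are scheduled.

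**Working it through.** **1. The passages side by side.** The protocol gives no figure on this point to reproduce, so the check begins with the text.

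- Repeated-measures model: individualized and standardized arms, four visits; control is not a level.
- ANOVA of 12-week change: groups not named. With two groups Tukey tests add nothing, so they suggest three groups, and the Table 2 analysis row fits that. It uses baseline and week 12 only.
- Control tests at weeks 4 and 8: scheduled under Testing and in Table 2, assigned to no analysis.

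**2. What each term estimates.** The stated model is

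Y_ijt = μ + arm_j + visit_t + (arm × visit)_jt + subject_i + e_ijt, with j = individualized or standardized.

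Let T_jt be the true training effect in arm j at visit t, and S_t the change that would have occurred without training. The expected change from baseline in arm j is T_jt + S_t.

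- Arm by visit: (T_1t + S_t) − (T_2t + S_t) = T_1t − T_2t. S_t cancels.
- Visit: (T_1t + T_2t)/2 + S_t. S_t remains in full, so the bias equals S_t.
- Exercise arm minus control: T_jt + (S_t in exercisers − S_t in controls). Only change truly common to both cancels.

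**3. Illustration of the visit test when training does nothing.** Sixteen per arm is the Sample size calculation figure before dropout (16/(1 − 0.2) = 20 after it); alpha is 0.05. All else is assumed: a shared change δ present at weeks 4, 8 and 12, and independent single-test error SD σ of 3% or 5%. With N participants in both arms, the noncentrality of the visit test is λ = N × 0.75 × (δ/σ)². For N = 32 this is 24(δ/σ)². For example, δ = 2% and σ = 3% give λ = 10.67. Simulated rejection rates (4,000 runs per cell, Greenhouse-Geisser correction):

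| Shared change | 16 per arm, σ = 3% | 16 per arm, σ = 5% | 20 per arm, σ = 3% | 20 per arm, σ = 5% |
|---|---|---|---|---|
| 0% | 4.6% | 4.5% | – | – |
| 1% | 22.3% | 9.8% | 28% | 11% |
| 2% | 76.0% | 31.3% | 86% | 39% |
| 3% | 98.7% | 63.5% | 100% | 77% |

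The noncentral F with 3 and 90 degrees of freedom, without the correction, gives 24%, 77% and 99% (σ = 3%) and 11%, 33% and 67% (σ = 5%) at 16 per arm, which agrees.

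A second simulation with another shape, a linear drift reaching 0.25, 0.5, 0.75, 1.0 or 1.5 within-person SDs by week 12, gave 12%, 38%, 75%, 95% and about 100%, against 5% with no drift. In both simulations the two-arm arm-by-visit test stayed at 4–6%.

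**4. Precision cost of a control contrast.** With equal group sizes n and change SD s, the before-after change in one arm has standard error s/√n, and arm minus control has s√(2/n). The ratio is √2 = 1.41. For σ = 3%, s = 3√2 = 4.24%; at n = 16 the standard errors are 1.06% and 1.50%.

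**5. The adherence rule.** Three sessions a week for 12 weeks is 36 sessions, and 70% of 36 is 25.2. Controls have no training sessions, so read literally the rule removes every one of them from analysis.

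**The case against.** The strongest reply is that the model fits its purpose. Research aims and the Abstract frame the time-course question as a difference between the two exercise groups, which the arm-by-visit term answers without bias. The main aim, incidence of response, does not use this model. The article never says that the visit effect will be read causally against no exercise. All of this stands. What remains is that the protocol names the effect of training as the target and fixes the factor levels. That is a stated choice, not a detail left to an analysis plan.

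Several stronger readings are tempting and not supported:

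- *The controls are unused.* Table 2 and the Tukey tests imply a comparison at 12 weeks. The gap is at weeks 4 and 8.
- *A control contrast would remove every shared influence.* The protocol does not say when controls are tested or where they are recruited, so season and referral-related regression to the mean need not be shared. Exercisers have resting BP and HR taken at every session, up to 36 times beyond the testing visits, so habituation is unequal. Fifteen experimental participants take the baseline tests twice, so familiarisation is unequal too.
- *The simulated rates show what will happen here.* They rest on assumed shifts and on no training effect at all. A control contrast keeps its nominal error in such a simulation because controls are given the same shift by construction.
- *The ±3% agreement window supports a 3% drift.* It is a tolerance between two bouts 20 minutes apart on the same day, not a mean change over weeks.
- *The magnitude-based inferences under Incidence of response share the fault.* The text does not say whether those effects are within-arm or against a comparator.

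**Conclusion.** The point holds in a limited form. The model named for the effect of training contains only exercising arms, its visit effect is an uncontrolled before-after change, and the control results at weeks 4 and 8 enter no stated analysis. The bias in a training effect read from the visit term equals the shared change, which the documents do not give. The rejection rates above show the mechanism and are illustrative only.

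A reader might infer that the randomised comparison of individualized with standardized prescription is compromised. It is not: shared change cancels from it. This is an inexpensive improvement to how training effects and their time course are reported, not a flaw in the trial's main comparison.

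**What to change.** 1. Keep the two-arm repeated-measures model for the arm-by-visit contrast, and state that its visit effect is not an estimate of the effect of training.
2. Add a repeated-measures model with three groups (individualized, standardized, control) that reports each exercise arm's change against control at weeks 4, 8 and 12. Label it non-randomised and supportive.
3. Amend the Table 2 analysis row to include time-course changes.
4. State that the rule on completed sessions and intensity adherence applies to exercisers only.

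The cost is one extra model and some wording; every control test is already scheduled. The downsides are wider intervals (about 1.41 times the single-arm before-after interval, if groups are of equal size and spread) and a contrast that removes only change truly shared with controls. The report should therefore state when controls were tested and where they were recruited, and mention the repeat baseline tests and the session-by-session resting measurements as limits.
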